### Consent and ethical considerations

Women planning to give birth at the Department of Obstetrics, Copenhagen University Hospital, Rigshospitalet have received written information about the study at one of their antenatal midwife consultations. When a parturient fulfils the inclusion criteria, she will be asked to participate in the study after receiving oral and written information from an investigator. In obtaining and documenting informed consent, the investigator will comply with any applicable regulatory requirements, and will adhere to ICH-GCP and the Declaration of Helsinki. The National Committee on Biomedical Research Ethics (approval number: H-4-2013-019) and the Danish Medicines Agency (approval number: EudraCT 2012-005782-12) have approved the study. The trial is registered at Clinicaltrials.gov (identifier: NCT01895218).

## Discussion

The aim of this study is to compare a new treatment option (iron isomaltoside 1000) to standard medical care. The choice of the latter active comparator, ‘the drug of first choice’, enables us to use the results of this study for assessing the potential additional benefit of iron isomaltoside 1000 in a clinical setting.

The standard medical care treatment group does not receive a general specified recommendation of oral iron supplementation. We considered that standard treatment, as defined by the individualised regimen chosen by the parturient and her midwife, was the proper comparator. A pregnant woman usually takes oral iron supplementation from early pregnancy and finds a preparation and a dose that is suitable for her. A general fixed regimen might cause gastrointestinal side effects in some individuals, and a possible insufficient effect in others. Therefore, the fixed regimen would be suboptimal as a comparator compared with the standard individualised regimen, which is current practice in the Capital Region of Denmark. The actual use of oral iron, including specific preparation, dose and duration of treatment, is registered at each follow-up visit.

The individualised regimen design implies that we were not able to blind the randomisation in this trial. Also, since iron tablets colour the stools, we assessed that a double-blinded design would be unfeasible and would not contribute additional scientific merit. Accordingly, most previously published randomised controlled trials with iron treatment of women after childbirth have not been double-blinded [23–27].

The strength of this trial is the fact that it will be conducted at a single centre. This means that the standard medical care is less diverse than it might otherwise be and we can ensure a full overview of all parturients with PPH ≥700 mL in the time period of inclusion, which will enable us to collect detailed information about those excluded and the reasons why not.

The risk of bias by selecting the subjective endpoint physical fatigue in an open-label study is an inherent weakness of the study. Fatigue is an important clinical endpoint that has consistently been shown to be affected by iron deficiency and iron deficiency anaemia. However, fatigue in the postpartum period is highly dependent on various attributes, including the mode and outcome of delivery, the duration of labour, medical comorbidities, the health of the infant and a host of social and environmental factors. Nevertheless, this design was previously used in a randomised controlled study in a similar population, where an open-label design and subjective primary endpoint were chosen for the most clinically relevant design [42].

The instrument used for measuring the primary endpoint is the physical fatigue subscale of the MFI. We selected this instrument due to its previous validation, including the findings of high feasibility and reliability in the postpartum population, specifically its use for measuring fatigue in parturients that experienced PPH. However, no validated questionnaires have been specifically developed for measuring postpartum fatigue. Although some available questionnaires for measuring fatigue have been validated for this population, they are all constructed to measure fatigue in other populations, often cancer or other chronic ill patients. Therefore, we developed a new questionnaire (PPQ) that is designed specifically to measure fatigue among puerperal women. A further objective of this study is to assess and validate its ability to measure fatigue in women after PPH.

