## Methods/Design

### Study design

The study will be a randomised, comparative, open-label single-centre study with a 1:1 allocation ratio. The trial is a company-sponsored interventional trial conducted according to International Conference on Harmonization-Good Clinical Practice (ICH-GCP) guidelines [34].

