### Inclusion criteria

Women, regardless of mode of delivery, will be eligible for inclusion in the study if they fulfil the following criteria: (1) they have signed the informed consent form, and (2) they have either (a) PPH ≥700 and ≤1,000 mL or (b) PPH >1,000 mL and Hb >6.5 g/dL (4.0 mmol/L) measured at >12 hours after delivery (Figure 1).

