### Number of participants

The following hypothesis will be tested: iron isomaltoside 1000 is superior to standard medical care in the treatment of iron deficiency in women with PPH with or without anaemia, measured primarily by a reduction in physical fatigue. The null hypothesis of no difference between the treatment groups will be tested against the alternative by constructing a two-sided 95% confidence interval of the difference in aggregated change in physical fatigue score from baseline to week 12 between the two treatment groups. The sample size calculations are based on the primary endpoint, aggregated change in physical fatigue score from baseline to week 12. A two-sided significance level of 5% is used and the power is set to 80%.

The use of the physical fatigue subscale of MFI allows a maximum change of 16 points. Based on clinical judgement and consensus between all authors, we wish to see a difference greater than 10% for claiming clinically relevant superiority. Hence, we set the minimal clinically relevant difference to 1.8. In a previous study, the standard deviation was found to be approximately 4.2 [40]. Therefore, 87 patients per treatment group are needed in order to demonstrate superiority. With a margin for missing data and a dropout rate of 13%, 200 women will be included.

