### Statistical methods and data analysis

All tests are pre-specified in a statistical analysis plan. The primary analysis population will be the full analysis set, including all randomised participants who received the study drug and have at least one post-baseline physical fatigue score. The primary endpoint is the aggregated change in the physical fatigue score from baseline to week 12. This will be calculated as the area under the curve of the changes in the physical fatigue score from baseline to each visit until week 12, divided by the number of scheduled days (observation period). The area under the curve will be calculated using the linear trapezoidal method and scheduled days. The primary endpoint will be analysed using an analysis of variance model, with treatment and amount of PPH (700 to 1,000 mL or >1,000 mL) as factors, and baseline MFI physical fatigue score as the covariate. The estimated treatment differences (iron isomaltoside 1000 versus standard medical care) expressed as contrasts of the adjusted means will be presented with corresponding 95% confidence intervals and the *P* value. Iron isomaltoside 1000 will be considered superior to standard medical care if the lower limit of the 95% confidence interval is above zero. We will also perform a per protocol analysis excluding participants with major protocol deviations, such as rescue allogeneic RBC transfusion.

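### Mode of delivery, which the article says affects postpartum fatigue, is in neither the stratification nor the primary model: the analysis stays valid, but a modest, cheap gain in precision and balance is passed up

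*Protocol article*

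**What the plan says.** Four places in the protocol article bear on this.

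- **Discussion**, in the paragraph on the weakness of a subjective endpoint in an open-label trial: "fatigue in the postpartum period is highly dependent on various attributes, including the mode and outcome of delivery". The sentence goes on to length of labour, the mother's other illnesses, the infant's health, and social and environmental influences.
- **Inclusion criteria**: "Women, regardless of mode of delivery, will be eligible for inclusion". Vaginal and caesarean births are therefore both enrolled.
- **Randomisation**: stratified by bleeding volume only, in two categories.
- **Statistical methods and data analysis**: the primary endpoint, the time-averaged change in physical fatigue to week 12, is analysed by a model "with treatment and amount of PPH (700 to 1,000 mL or >1,000 mL) as factors", with the baseline physical fatigue score as covariate.

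The article states no primary or supportive analysis that includes mode of delivery. Because it sets out the terms of the primary model, the point concerns a stated choice and not a detail left to the statistical analysis plan.

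**The concern.** Mode of delivery is settled before randomisation, is objectively recorded, and cannot be altered by the allocated treatment. By the article's own account it belongs to a group of attributes that strongly influence the outcome. A baseline variable of that kind is the usual candidate for covariate adjustment. If it predicts the endpoint beyond the terms already fitted, leaving it out puts explainable variation into the error term and widens the confidence interval. A chance difference between arms in the share of caesarean births would also pass into the unadjusted estimate.

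At stake is efficiency, and how persuasive the result is if the arms turn out unbalanced on mode. Adjustment chosen only after seeing such an imbalance would be open to challenge; adjustment fixed beforehand would not.

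**Working it through.** **Inputs from the article** (Number of participants; Study design): two-sided alpha 0.05, power 80%; "we set the minimal clinically relevant difference to 1.8"; "the standard deviation was found to be approximately 4.2"; 1:1 allocation; 87 per group; 13% dropout; 200 in total.

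**Inputs assumed, because the article gives none:** the partial R² of mode of delivery given the terms already in the model (2% to 15%); the correlation of baseline score with endpoint (0.5, in step 3 only); the caesarean share (20% to 50%); the difference between modes on the endpoint (1 to 3 points).

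**1. The plan's own figure.** Normal approximation: n = 2 × [4.2 × (1.960 + 0.842) / 1.8]² = 85.5, so 86 per group. The two-sample t version gives 86.4, so 87, as stated. For dropout, 174 / (1 − 0.13) = 200, as stated. Power at 87 per group is 80.3% (t).

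**2. Gain if 4.2 is the residual SD.** The residual SD becomes 4.2 × √(1 − R²), and the noncentrality is 1.8 / [SD × √(2/87)]. The present model leaves 174 − 4 = 170 degrees of freedom, and one more factor leaves 169.

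| Assumed partial R² | Residual SD | Power | Gain (points) | 95% CI half-width |
|---|---|---|---|---|
| 0 | 4.200 | 80.25% | 0.0 | 1.25 |
| 0.02 | 4.158 | 81.03% | 0.8 | 1.24 |
| 0.05 | 4.094 | 82.21% | 2.0 | 1.22 |
| 0.10 | 3.984 | 84.20% | 3.9 | 1.18 |
| 0.15 | 3.872 | 86.18% | 5.9 | 1.15 |

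Subtracting powers already rounded to one decimal gives 0.7 in place of 0.8 in the second row (81.0 − 80.3) and 1.9 in place of 2.0 in the third (82.2 − 80.3). At R² = 0.10 the equivalent sample is 87 / 0.90 = 96.7 per group, about 10 more women per arm.

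**3. Gain if baseline adjustment has already reduced the SD.** The article does not say that 4.2 is a baseline-adjusted SD. If it is unadjusted and the baseline correlation is 0.5, the residual SD before adding mode is 4.2 × √(1 − 0.25) = 3.64, and power at 87 per group is already about 90%. Multiplying that SD by √(1 − R²) gives:

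| Assumed partial R² | Residual SD | Power | Gain (points) |
|---|---|---|---|
| 0 | 3.64 | 90.1% | 0.0 |
| 0.02 | 3.60 | 90.6% | 0.6 |
| 0.05 | 3.55 | 91.5% | 1.4 |
| 0.10 | 3.45 | 92.8% | 2.7 |

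**4. Price if mode explains nothing.** One degree of freedom is spent (170 to 169). The expected variance rises by a factor of 169/168 = 1.006, about 0.6%. In the power calculation the lost degree of freedom leaves power at 80.3%.

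**5. Chance imbalance.** The SD of the between-arm difference in caesarean share is √[p(1 − p) × 2/87]. This is 0.061 at p = 0.2 and 0.076 at p = 0.5. A difference of 10 percentage points or more then arises in about 10% to 19% of randomisations.

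- With modes 1 to 3 points apart on the endpoint, a 10-point imbalance shifts the unadjusted estimate by 0.10 × (1 to 3) = 0.1 to 0.3 points.
- At the 95% limit (1.96 SD) the imbalance is 0.119 at p = 0.2 and 0.149 at p = 0.5. The shift runs from 0.119 × 1 = 0.12 to 0.149 × 3 = 0.45 points, which is 7% to 25% of 1.8.

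**The case against.** The strongest reply is that nothing here is wrong. A model with treatment, the stratification factor and the baseline score is standard and valid, and its confidence interval already allows for random imbalance in unlisted covariates. That stands, and it makes this an improvement and not the correction of an error.

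The reply also has force on the premise. The Discussion sentence belongs to a passage on limitations and lists several attributes together. A reader might infer from the order of the list that mode of delivery is the most important one, or that it stays a strong predictor after baseline adjustment. The text ranks nothing, and it does not address change from baseline given the baseline score. Nor does the article describe recovery separately by mode, so it cannot be said that a baseline score taken after delivery fails to carry the effect; it may well absorb part of it. The same sentence could support other covariates. Mode is singled out because it is objective, known before randomisation, and costs one parameter as a two-level factor.

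The last objection is timing. Trial status gives a first inclusion in May 2013 and expected completion of inclusion in August 2014; the article appeared in January 2015. A late change of primary model in an open-label trial invites suspicion of a data-driven choice. This is a fair condition on how the change is made. It is met if the change is documented before database lock, made without sight of outcomes by arm, and reported beside the present model.

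**Conclusion.** The point holds as a minor efficiency improvement. The article names mode of delivery among the influences on its primary outcome, enrols all modes, and uses mode in neither the randomisation nor the primary model.

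A reader might go further and infer that the omission biases the treatment comparison, inflates the type I error or leaves the trial underpowered. The documents support none of these. Randomisation protects the comparison, and the 87 per group and 200 in total reproduce from the stated inputs without this covariate.

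The benefit is modest and cannot be quantified from the article. Over an assumed partial R² of 2% to 10% it is about 0.8 to 3.9 power points with 4.2 as the residual SD, or about 0.6 to 2.7 points under an assumed baseline correlation of 0.5. Protection against imbalance is of similar weight: a shift of at most about 0.45 points at the 95% limit under the assumed inputs, against a confidence interval half-width of 1.25. The case for acting is that the cost is close to nil even if mode turns out to explain nothing.

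**What to change.** In Statistical methods and data analysis, add mode of delivery (for example vaginal versus caesarean) as a pre-specified fixed factor in the primary model, beside treatment, bleeding category and baseline score. Keep the present model as a stated sensitivity analysis. Make the change before database lock, by a dated amendment recording that no outcome data by arm were consulted.

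The cost is one degree of freedom out of about 170, the amendment, and one variable. That variable is assumed to be available from the obstetric delivery record, since the article does not list the case report form fields. The sample size does not change.

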## Trial status

The trial was initiated and the first parturient was included in May 2013. Inclusion and randomisation are ongoing and expected to be finished in August 2014.

## Abbreviations

CRA: clinical research associate
EPDS: Edinburgh Postnatale Depression Scale
Hb: haemoglobin
HELLP: haemolysis, elevated liver enzymes, and low platelet count
ICH-GCP: International Conference on Harmonization – Good Clinical Practice
MFI: Multidimensional Fatigue Inventory
PPH: postpartum haemorrhage
PPQ: Postpartum questionnaire
RBC: red blood cells.
